# *Genotype of M. pneumoniae*

See Aim I, chapter 3. The genotype of *M. pneumonia*e will be determined in each positive sample.

### Study population

## *Population*

Group A+/HAP+: children, aged 0-16 years tested positive for *M. pneumoniae* in group A/HAP by culture or PCR (we expect to find 10% *M. pneumoniae* positive RTI).

Group B+: children, aged 0-16 years tested positive for *M. pneumoniae* in group B by PCR or culture (we expect to find 10% of these children to be positive by PCR).

## *Inclusion criteria*

Group A+/HAP+

Eligible for group A/HAP

Real-time PCR or culture positive for *M. pneumoniae*

Written informed consent for receiving results of the *M. pneumoniae* tests.

Written informed consent for group A/HAP and A+/HAP+

Group B+

Eligible for group B

Real-time PCR or culture positive for *M. pneumoniae*

Written informed consent for receiving results of the *M. pneumoniae* tests.

Written informed consent for group B and B+

## *Exclusion criteria*

Group A+/HAP+

Non-eligible for group A/HAP

Real time PCR or culture negative for *M. pneumoniae*

No written informed consent for receiving results of the *M. pneumoniae* tests.

No written informed consent for group A+/HAP+

Group B+

Not eligible for group B

Real time PCR or culture negative for *M. pneumoniae*

No written informed consent for receiving results of the *M. pneumoniae* tests.

No written informed consent for group B+

## *Sample size calculation*

This study will be merely descriptive. Currently, about 10% of the enrolled children are tested positive by PCR for *M. pneumoniae*. This ancillary study will commence halfway during the original study, so we expect in total an additional 50 children will be tested positive by PCR and will therefore be eligible for this study.

### Study Methods

*Additional visits for follow up*

Group A+/HAP+ and B+ will be asked to return for a maximum of 12 follow-up visits after visit 1. For convenience of participants, house calls will be offered to each participant and their parents and performed by the research team. During these visits a nasopharyngeal lavage and an oropharyngeal swab will be taken and there will be additional short questionnaires.

### Statistics

*Research question(s)*

Does the presence of *M. pneumoniae* in healthy individuals at a certain time point reflect a persistent carriage stage or merely an increasing or declining bacterial load before or after an infection?

*Analysis*

Bacterial load will be determined in samples taken from each visit. These will be used mainly in a descriptive fashion. We hypothesize that a persistent carriage stage does not exist and expect to find clearance of bacteria in all patients eventually. The number of RTI will be scored in each group. The time to clear all bacteria (defined by a negative PCR) will be determined for each individual and means will be compared between each group. The genotype of *M. pneumoniae* will be determined in every sample to compare to ‘time to clear’ and severity of infections.

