In addition, we will study the role of bacterial and viral co-infections. Co-infections can account for up to 30-50% of the cases of M pneumoniae infection. (4, 15, 16) Infection with M. pneumoniae is frequently associated with infections with S. pneumoniae and respiratory viruses. This association might be due to damage to the respiratory epithelium by a virus facilitating infection with M. pneumoniae. However, virtually nothing is known regarding this issue. Children younger than 5 years frequently suffer from viral respiratory infections, which might support the data that M. pneumoniae infections in this age-group are more frequent than previously thought. It is also unknown whether viral co-infection leads to more severe clinical disease. This study aims to answer these questions.

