## Study procedures

Visit 1:

From each patient the following samples will be obtained

- Oropharyngeal swab
- Nasopharyngeal swab
- Nasopharyngeal lavage
- Serum (blood sample of 200 microliters)

Patients from group A will have their samples taken during their visit at the Emergency Department/HAP. In those cases many of the samples are taken for diagnostic reasons anyway. Samples can usually be split for clinical (diagnostic) and research purposes. This will minimize the burden for the patients.

Patients from group B are at the day care ward for surgical treatment. The blood sample will be drawn from the vena puncture, which is conducted by the anaesthesiologist, in order to obtain iv-access for administration of anaesthetics drugs. The other samples are taken after the patient has had their anaesthetics.

Patients from both groups fill out a short questionnaire about their health (history, use of antibiotics, smoking, attendance of day care centre, etc)

Visit 2:

Group A will be asked to return for a follow-up visit, 3 tot 4 weeks after their initial visit. During this visit another blood sample will be taken and there will be another short questionnaire.

Group B will not have to return to hospital. They will be phoned by a member of the research team to check if there were any respiratory tract infections in our healthy control or his/her family since the day of surgery.

Withdrawal of individual subjects

Subjects can leave the study at any time for any reason if they wish to do so without any consequences. The investigator can decide to withdraw a subject from the study for urgent medical reasons.

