# Ancillary studies

## Ancillary study 1: Follow-up study to investigate carriage.

### Rationale

Preliminary data from the original MymIC study have shown the presence of *M. pneumoniae* in the respiratory tract of healthy individuals. In addition, the actual bacterial load (determined by real-time PCR) in patients with a RTI seems to be higher than in healthy individuals. These data suggest that asymptomatic colonization with *M. pneumoniae*, defined as a single positive test for *M. pneumoniae* at a certain timepoint, exists. This now leaves room for two options: (1) presence of *M. pneumoniae* in a healthy individual is always associated with an RTI either before or after, reflecting an increasing or declining load, or (2) the presence of *M. pneumoniae* reflects a persistent carriage stage without resulting in infection. At this moment there is no evidence for either of these possibilities and very little is known about *M. pneumoniae* carriage. In this study we will address this issue by performing follow up sampling in both participants with an RTI caused by *M. pneumoniae* and healthy participants with a positive *M. pneumoniae* test (either culture or PCR). The bacterial load and genotype*,* found in these follow-up samples will be related to clinical data in a descriptive manner.

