### Study design

## *Approach*

Children enrolled in the study as described under Aim I in chapter 3, may participate in the follow up study if they tested positive for *M. pneumoniae* by either real time PCR or culture in a sample taken during the first visit. The results of the tests taken during the first visit will be made available to parents and participants about one week prior to the second visit. Subsequently they will be asked to participate in the following protocol

*Definitions*

1. Children with RTI in combination with the presence of *M. pneumoniae,* as detected by either culture or real-time PCR in either the oropharyngeal swab or the nasopharyngeal lavage taken during the first visit, i.e. **group A+** or **group HAP+**. (Note: these children not necessarily suffer from disease caused by infection with *M. pneumoniae*. The gold standard for *M. pneumoniae* infection in this study is serology in combination with standard PCR.)

2. Healthy children tested positive for *M. pneumoniae* by culture or real-time PCR in either the oropharyngeal swab or the nasopharyngeal lavage taken during the first visit, i.e. **group B+**.

*Follow up protocol*

In the follow up protocol participants will be tested for the presence of *M. pneumoniae* in the nasopharynx and oropharynx once a month during a maximum period of one year or until they test negative in both tests (culture and real-time PCR) on two successive occasions. For monthly sample collections, either house-calls will be performed or participants may visit the emergency department of the Erasmus MC – Sophia, whichever is most convenient for participants at that time. If a child, participating in this study, suffers from a RTI during the follow up period, he/she will be evaluated, during daytime, by a physician specialized in pediatric infectious diseases. At all times during the follow up study, parents are free to take him/her to their own general practitioner. For emergencies parents should follow the normal procedures.

*Clinical samples*

Each month a nasopharyngeal lavage and an oropharyngeal swab will be taken and real-time PCR and culture will be performed for *M. pneumoniae* as described previously in chapter 3. Test results will be made available to the participants and their parents every month since these results determine whether the study is continued for each participant individually.

*Clinical data*

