Each visit, information about RTI (both participant as well as siblings and parents), use of antibiotics, hospitalization, complications and vaccinations in the previous month will be recorded in a standardized questionnaire.

*Detection of M. pneumoniae*

See Aim I, chapter 3

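### The ancillary study's raw RTI count per group mixes background RTIs and length of carriage with any effect of M. pneumoniae, so it cannot by itself support or refute a link between a positive test and an RTI

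*Protocol*

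**What the plan says.** Section 12.1.1 sets out two options for a healthy child who tests positive. Under the first, the finding "is always associated with an RTI either before or after, reflecting an increasing or declining load"; under the second, it is persistent carriage without infection. Section 12.1.6 asks whether the finding does "reflect a persistent carriage stage or merely an increasing or declining bacterial load before or after an infection". The analyses listed there are serial bacterial load (mainly descriptive), the RTI count ("The number of RTI will be scored in each group"), time to clear with means compared between groups, and genotype. No cause, denominator or time window is given for the RTI count.

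The design in 12.1.3 and 12.1.4 fixes what that count can contain:

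- **Who is followed.** Enrolled children "may participate in the follow up study if they tested positive for *M. pneumoniae* by either real time PCR or culture" in a first-visit sample. Negative children are excluded under 12.1.4.
- **For how long.** Sampling is monthly, for at most one year or "until they test negative in both tests (culture and real-time PCR) on two successive occasions".
- **How RTIs are recorded.** A questionnaire at each visit collects "information about RTI (both participant as well as siblings and parents), use of antibiotics, hospitalization, complications and vaccinations in the previous month". A child with an RTI is also to be seen by a paediatric infectious disease physician, but no test for cause is specified.
- **What is sampled.** A lavage and an oropharyngeal swab, tested for M. pneumoniae. No serum or viral PCR is planned, although 12.1.3 names serology with standard PCR as the gold standard for M. pneumoniae infection.

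Separately, section 7.3 plans a telephone call to every group B child, positive or negative, "to check if there were any respiratory tract infections in our healthy control or his/her family since the day of surgery".

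**The concern.** An RTI count per group reads naturally as evidence on the first option: many RTIs among positive healthy children would suggest that a positive test goes with infection. Three features of the design prevent that reading.

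1. **Any cause counts.** Section 1 says "Children younger than 5 years frequently suffer from viral respiratory infections", and section 4.1 plans 400 of 500 children (80%) under 5 in each group. Without serum, a follow-up RTI cannot be classified by the protocol's own gold standard.
2. **No background rate.** With no negative child in follow-up, there is nothing against which to judge an excess of RTIs.
3. **Observation time depends on clearance.** A child who carries longer is watched longer and collects more RTIs. The RTI count is thus tied mechanically to time to clear, the other outcome compared between groups.

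Ordinary colds could then be credited to M. pneumoniae, and a group difference in RTIs could reflect only a difference in length of follow-up.

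**Working it through.** **The plan's own figure.** Section 12.1.4 expects 50 further positive children. From 500 + 500 children (4.1), a start halfway through enrolment and about 10% positive (12.1.4): (500 + 500) × 0.5 × 0.10 = 50. This reproduces. The group B share is 500 × 0.5 × 0.10 = 25.

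**Range of observation.** The shortest path is two successive negative monthly visits, about 2 months. The longest is 12 months.

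**Assumption.** The protocol gives no RTI rate. Take a constant any-cause rate r per child-year, unrelated to M. pneumoniae. Then expected RTIs per child = r × m/12, and the chance of at least one = 1 − exp(−r × m/12), for m months observed.

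| Assumed r per year | At least one RTI, 2 months | At least one RTI, 12 months | Of 25 B+ children |
| --- | --- | --- | --- |
| 1 | 15% | 63% | about 4 vs 16 |
| 3 | 39% | 95% | about 10 vs 24 |
| 6 | 63% | 99.8% | about 16 vs 25 |

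Follow-up length alone moves the proportion by about 37 to 56 percentage points.

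**Group comparison.** With r = 4, a group observed 4 months on average scores 4 × 4/12 = 1.3 RTIs per child, and one observed 8 months scores 4 × 8/12 = 2.7. Per child-month both give 4/12 = 0.33, the correct answer of no difference.

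**Could chance RTIs pass for the first option?** Take one month either side of the positive test. At r = 3 to 8, 1 − exp(−r × 2/12) gives 39% to 74%. Controls must, however, be free of RTI beforehand, for one week (4.2) or two (section 3). Removing one week from the window gives 36% to 69%; removing two gives 32% to 64%. The first option says that an RTI is always present. Even at 74% per child, the chance that all 25 have one is 0.736^25, about 0.0005. Over a full 12 months it is 0.950^25 = 0.28 at r = 3, and (1 − exp(−6))^25 = 0.94 at r = 6. Chance RTIs can therefore mimic the first option in children followed for many months, but not in a short window.

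**What the telephone call could show.** At 10% positive, the second half of group B gives 25 positive and 225 negative children; all of group B gives 50 and 450. Suppose 22% of negative children report an RTI (r = 1 over 3 months; the true interval is not stated). With 80% power at two-sided 5%, the detectable difference is about 27 points for 25 versus 225, and about 19 points for 50 versus 450.

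**The case against.** The strongest reply is that section 12.1.6 does not make the RTI count the test of the first option. The question is put in terms of load; load, culture and genotype are measured monthly; and the hypothesis that all children eventually clear is addressed by time to clear. Section 12.1.4 calls the study purely descriptive. This stands. A reader might infer that the ancillary study as a whole cannot show whether a positive test precedes infection. The documents do not support that, because a rise in load dated against an RTI, or clearance with no RTI during follow-up, is informative for the individual child.

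A reader might also infer that most positive healthy children will have an RTI close to the test by chance, so that the first option would seem confirmed. That is not supported at the lower assumed rates, and the required RTI-free period lowers the figure further. Because that option says always, a positive child without any RTI counts against it.

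It can also be said that a denominator is a matter for an SAP, which is not shown. In part that is fair: the wording does not forbid reporting per child-month. But the protocol itself fixes the population, the stopping rule, the samples and the use of a count. Calling the analysis descriptive does not help, since a descriptive count misleads just as easily when observation time differs.

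The telephone call is an imperfect comparator, and the physician evaluation is a second clinical source for RTIs. Neither establishes cause.

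**Conclusion.** The concern holds for the RTI count and not for the ancillary study as a whole. As worded in 12.1.6, the count combines background RTIs, length of carriage and any effect of M. pneumoniae, and cannot by itself support or refute the option that a positive test in a healthy child is linked to an RTI. Under a constant background rate, doubling observation time doubles the count (1.3 to 2.7 per child at 4 per year) with no true difference. The premises come directly from 12.1.3, 12.1.4 and 12.1.6; the sizes rest on assumed any-cause rates of 1 to 8 per child-year, constant over time. The direction does not depend on the rate chosen. The wording should be changed, since the data needed are already planned.

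**What to change.** Amend section 12.1.6 as follows.

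1. Replace the raw count with RTIs per child-month of observation, or with RTIs in a fixed window common to all children.
2. As a background comparison, use the call already planned for all of group B. Compare the child's own RTI since surgery, separate from the family's, between B+ and test-negative children, by age group (under 5; 5 and over) and allowing for the interval to the call. State its limits: any cause, forward-looking only, call date not fixed, and families of positive children may already know the result, because 12.1.3 releases results about a week before the second visit. It is also imprecise, as the detectable differences above show.
3. Describe each follow-up RTI beside the load before and after it, whether rising or declining, and report RTIs with negative adjacent samples separately. Do not make a rise in load the only criterion for a link: the first option in 12.1.1 includes a declining load after an earlier RTI, and such a child has no earlier sample from which a rise could be shown.

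The cost is a little more analysis, recording the call date and keeping the child's answer apart from the family's. No extra visit, sample or participant is needed. The background question will still be answered only approximately.

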# INTRODUCTION AND RATIONALE

# Lower respiratory tract infections (LRTIs) are among the most common infections in children and adults. The World Health Organization estimates there are 150.7 million cases of pneumonia each year in children younger than 5 years, with as many as 20 million cases severe enough to require hospital admission. Respiratory tract infections are the number one killer in children in developing countries. (1) In children with lower respiratory tract infections, M. pneumoniae is the second most common cause of LRTI after Streptococcus pneumoniae. (2) M. pneumoniae is a human pathogen that causes a range of respiratory infections, such as tracheobronchitis, pharyngitis, and atypical pneumonia. Up to 40% of community-acquired pneumonias are caused by M. pneumoniae and as many as 34% of cases requiring hospitalization in children. (3, 4) Glomerulonephritis, carditis, rhabdomyolysis, Bell palsy, Guillain-Barre syndrome, and acute transverse myelitis are rare complications of M. pneumoniae infection. In addition, infection with M. pneumoniae is associated with both chronic stable asthma and acute exacerbations of asthma. (5) Infection with M. pneumoniae is therefore a major burden of disease. This study has three objectives.

1. A specific diagnosis of the cause of LRTI is important because β-lactam antibiotic treatment of M. pneumoniae infections is ineffective, due to the lack of a cell wall, whereas the use of antibiotics such as macrolides can markedly reduce the duration of the illnesses. (6) While the clinical diagnosis of LRTI is usually relatively straightforward, determining the etiological diagnosis can be much more difficult due to the limitations of conventional diagnostic tests, and because of difficulty in obtaining adequate sputum samples for culture in children. As culture of M. pneumoniae is slow and insensitive, the laboratory diagnosis has largely relied on serological testing. Although there have been recent improvements, the sensitivity and specificity of antibody detection is suboptimal. In addition, it often only provides a retrospective diagnosis of acute infection because a convalescent serum specimen is needed to show a fourfold increase in titre. Serologic testing is therefore not optimum for patient management, however this is still used as golden standard for M. pneumoniae detection. (7)

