More recently, polymerase chain reaction (PCR) demonstrated the potential to produce rapid, sensitive and specific results, and is now considered the method of choice for direct pathogen detection. (8) However, there is justified concern when the PCR assay is used as the sole means of detection without culture, serology, or clinical data, because surveillance studies using culture and/or PCR indicate that a prolonged asymptomatic carrier state may occur in some persons. (9-12) Since it is not known whether there is a specific threshold quantity of M. pneumoniae in respiratory tract tissues that can differentiate asymptomatic carrier state from infection, a positive result by PCR may overestimate the clinical importance, and may result in unnecessary use of antibiotics. On the other hand, if quantitative PCR will demonstrate to be a reliable technique for diagnosing M. pneumoniae infection, M. pneumoniae will be diagnosed more often. This will result in more adequate treatment of RTI’s in children. It has been suggested that children colonized with M. pneumoniae might be an unrecognized reservoir for the spread of this pathogen. (12) The application of quantitative PCR assays will be crucial in optimizing diagnosing RTI by M. pneumoniae, and in gaining a better understanding of the carrier state associated with M. pneumoniae. Therefore, this is one of the main objectives of our study.

1. M. pneumoniae is thought to be a pathogen that causes pneumonia in children aged 5 years and older. Choice of treatment is based on this supposed age-distribution. Since M. pneumoniae is not susceptible to β-lactam antibiotics, a macrolide antibiotic is the first choice treatment in this age-group. In children younger than 5 years, β-lactam antibiotics are the first choice treatment, because M. pneumoniae is presumed to be a rare cause of RTI in this age-group. However, data on age distribution are conflicting. (13) Specialized diagnostic techniques showed that M pneumoniae might have a more important role in causing both upper and lower respiratory tract infections than previously thought; they seem to be frequent also in children aged less than 5 years. (4, 14) To address this issue, we will investigate the rate of infection among children belonging to different age groups.

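### The ancillary time-to-clear comparison pools children who did and did not receive an antibiotic active against M. pneumoniae

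*Protocol*

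**What the plan says.** The ancillary study asks, of healthy children who test positive, whether the finding means lasting carriage or a load that is rising or falling around an infection (Protocol section 12.1.6, research question). The analysis paragraph of that section states the expectation: "We hypothesize that a persistent carriage stage does not exist and expect to find clearance of bacteria in all patients eventually". It then fixes the comparison: "The time to clear all bacteria (defined by a negative PCR) will be determined for each individual and means will be compared between each group". Genotype is the only factor that it sets against time to clear.

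Elsewhere the protocol bears on antibiotics as follows.

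- Section 12.1.3 (Clinical data) collects exposure: "Each visit, information about RTI (both participant as well as siblings and parents), use of antibiotics, hospitalization, complications and vaccinations in the previous month" goes into a standardised questionnaire. Section 3 (Clinical data) also documents antibiotic use and treatment for the main study.
- Section 12.1.1 says that load and genotype in the follow-up samples will be related descriptively to clinical data, without naming antibiotics.
- Section 4.3 excludes recent antibiotic use in both groups, but only before enrolment. No rule covers antibiotics started at or after visit 1.
- Section 1 states that "the use of antibiotics such as macrolides can markedly reduce the duration of the illnesses" and that, for children of 5 years and older, "a macrolide antibiotic is the first choice treatment in this age-group". Below 5 years it names β-lactams as first choice, to which the organism is not susceptible.
- Section 12.1.3 (Clinical samples) says: "Test results will be made available to the participants and their parents every month".

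**The concern.** Children in A+/HAP+ enter with symptoms for which an antibiotic may be prescribed. Children in B+ enter well. If an active antibiotic brings PCR negativity forward, the two group means differ even when clearance without treatment is the same in both. A reader of the result would attribute that difference to disease state.

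A second, separate issue concerns the healthy carriers, who are the subject of the research question. If a B+ child is treated during follow-up and then tests negative, the plan counts that child as cleared. The hypothesis that persistent carriage does not exist is judged by whether everyone clears, so such a child adds to the apparent support for it without showing what would have happened untreated.

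**Working it through.** **1. Size of the study.** Section 12.1.4 expects 50 additional positive children. With about 10% positive, 500 + 500 children in the main study (section 4.1) and half of recruitment remaining, 0.10 × 1000 × 0.5 = 50. The figure reproduces. With the 10% expected in each group, that is 0.10 × 500 × 0.5 = 25 per group.

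**2. Spurious difference in means.** Suppose natural clearance has the same mean m in both groups, and an active antibiotic lowers a treated child's mean by D. With treated shares pA and pB:

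mean A = m − pA × D; mean B = m − pB × D; so B − A = (pA − pB) × D.

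The documents give none of pA, pB or D. They say that macrolides shorten illness, not that they bring forward a negative PCR. Everything below is therefore assumption.

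**3. What the age mix suggests for pA.** Group A is 400 children under 5 and 100 aged 5 or over. Suppose every older positive child, and no younger one, received a macrolide.

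- Equal positivity: pA = 100/500 = 20%.
- Positivity of 10% and 22% (section 4.4: 10% plus the 12% detectable difference): 0.10 × 400 = 40 and 0.22 × 100 = 22, so pA = 22/62 = 35%.

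This is a reference case, not a bound: younger children may receive a macrolide, and older ones may not.

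Assume m of 2 or 4 months, cut to a half or a quarter. Then D = 1, 1.5, 2 or 3 months, and B − A in months is:

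| pA | pB | D = 1 | D = 1.5 | D = 2 | D = 3 |
|---|---|---|---|---|---|
| 20% | 10% | 0.10 | 0.15 | 0.20 | 0.30 |
| 20% | 0% | 0.20 | 0.30 | 0.40 | 0.60 |
| 35% | 10% | 0.25 | 0.38 | 0.51 | 0.76 |
| 35% | 0% | 0.35 | 0.53 | 0.71 | 1.06 |

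**4. Simulation with larger treated shares.** Settings: 25 children per group, the same exponential natural clearance in both, monthly sampling capped at 12 months, 20,000 repeats, and a Welch-type comparison at a nominal 5%. The protocol names no test, so the rejection rate only gauges the bias against sampling noise.

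| m, D (months) | 30% vs 0%: difference, rejection | 60% vs 10%: difference, rejection |
|---|---|---|
| 2, 1 | 0.29, 8.5% | 0.48, 16.1% |
| 2, 1.5 | 0.41, 12.8% | 0.69, 32.0% |
| 4, 2 | 0.53, 8.9% | 0.88, 17.8% |
| 4, 3 | 0.82, 15.0% | 1.36, 37.8% |

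With no antibiotic effect, or with 60% treated in both groups, the difference is essentially zero and rejection is about 5%. The simulated differences track step 2 (0.3 × 1 = 0.30 against 0.29). Where m is long they fall below it (0.5 × 3 = 1.5 against 1.36), because of the monthly visits and the cap.

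**5. The carriage question.** This depends on B+ alone. Suppose 20% of 25 B+ children would never clear naturally (5 children), and treatment always clears them. If a share q of them is treated, 5 × (1 − q) remain uncleared: 5.0, 4.5, 3.5 and 2.5 children for q of 0, 10%, 30% and 50%. Treating A+/HAP+ children does not change this count.

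**The case against.** The strongest reply is that the protocol does not overlook antibiotics. It records their use monthly and foresees relating load to clinical data, and the handling of a recorded covariate often sits in an analysis plan, which is not at hand. This stands against any claim that the study as a whole disregards antibiotics. It does not answer the narrower point: section 12.1.6 itself fixes the comparison of means and names genotype, but not antibiotics, as a factor.

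Second, four fifths of group A is planned to be under 5, where β-lactams are first choice. This stands. It argues for a modest exposure gap and against assuming that most A+/HAP+ children receive an active drug.

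Third, the study is called merely descriptive and states no alpha or power. That lowers the weight of the point, but a described mean is confounded in the same way as a tested one.

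A reader might go further and infer that the plan takes treated clearance for natural clearance, and so manufactures evidence against persistent carriage. The documents do not support that. No sentence says that the two will be interpreted alike. Treatment of A+/HAP+ children affects only the group contrast. In B+ the effect needs treated B+ children: monthly disclosure of results and access to a general practitioner make this possible, but nothing states that well carriers will be treated. Nor does it follow that the two explanations in section 12.1.1 become indistinguishable, because load, respiratory infections and antibiotic use are collected for each child.

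**Conclusion.** The point holds in limited form. The comparison in section 12.1.6 pools treated and untreated children although exposure probably differs between A+/HAP+ and B+, so the difference in mean time to clear can partly reflect treatment. Separately, any B+ child treated during follow-up would count as a clearance on the same terms as a spontaneous one.

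The size cannot be derived from the documents. Across the assumed ranges shown, the A+/HAP+ group appears to clear about 0.1 to 1.4 months sooner with no true difference. The upper end needs 60% against 10% treated, which nothing in the protocol supports; the age-based reference case stops at about 1.1 months. The bias vanishes if antibiotics do not speed PCR clearance or if exposure is equal. This is a worthwhile, inexpensive correction to a descriptive ancillary study and does not touch the main study.

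**What to change.** In section 12.1.6:

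- Report time to clear by group separately for children with and without an antibiotic active against M. pneumoniae between visit 1 and clearance.
- Base statements about persistent carriage on untreated B+ children, and list treated B+ children individually with their months positive before treatment.
- Keep the all-children comparison as secondary.
- Optionally add a sensitivity analysis that censors at the first active antibiotic. It needs a time-to-event summary, because simple means do not handle censored times. It should note that censoring may be informative, since treatment tends to follow symptoms.

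The split is itself descriptive: a child who clears slowly has more time in which to be treated, so the untreated subgroup leans towards early clearance. This should be said next to the result.

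The cost is a few sentences and small subgroups among about 50 children, hence less precision. No new visits or samples are needed. The protocol says only that antibiotic use is recorded, so the team should confirm that the questionnaires capture which drug was taken and when.
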